### Biological Sample Collection

Saliva and stool samples were self-collected at participants’ residences and couriered back to the study site by a designated, reliable, and licensed courier trained to respect the *cold chain* to maintain sample integrity. Biological samples are being stored at –80 °C at an appropriately regulated tissue repository until the planned batch analyses at the end of the study. This strategy required comprehensive collection kits to be sent to participants, which included a clear, illustrated, and concise manual, as well as items to alleviate any concerns about needing to store the biological samples in their freezer between the time of collection and courier pickup. These items included laboratory-grade biohazard bags and additional containers to contain the biohazard bags to have multiple degrees of separation between the collected biological sample and the food items in the freezer.

### Monitoring and Safety Reporting

Monitoring was carried out periodically by an external, independent monitor. This allowed the evaluation of the trial progress, verification of the accuracy and completeness of electronic case report forms, and resolution of any inconsistencies in the trial records, as well as ensured that all protocol requirements, applicable local laws, International Council for Harmonisation of Technical Requirements for Pharmaceuticals for Human Use [38] guidelines, and investigator obligations were fulfilled.

Safety reporting was conducted in accordance with a preagreed study safety monitoring plan. All adverse and serious adverse events were recorded in the study database.

### Statistics

This is an exploratory study of the effect of BL NCC3001 on mood in pregnant and postpartum women; therefore, effect sizes are unknown. However, illustrative power calculations are shown in Table 2. Once completed, this trial will allow a potential follow-up trial to be designed and powered properly, where observations could be confirmed.

**Table 2 table2:** Illustration of error rates and statistical power for the Edinburgh Postnatal Depression Scale (EPDS) and State-Trait Anxiety Inventory (STAI) over 1000 simulations.

Outcome and hypothesis		Comparison	Max-*t* test^a^, %
**EPDS**			
	Null	Prepartum + postpartum probiotic vs placebo control	1.70
	Null	Postpartum-only probiotic vs placebo control	1.60
	25% difference	Prepartum + postpartum probiotic vs placebo control	72.00
	25% difference	Postpartum-only probiotic vs placebo control	48.10
**STAI**			
	Null	Prepartum + postpartum probiotic vs placebo control	2.20
	Null	Postpartum-only probiotic vs placebo control	1.30
	25% difference	Prepartum + postpartum probiotic vs placebo control	69.20
	25% difference	Postpartum-only probiotic vs placebo control	50.30

^a^Rows where the hypothesis is null display the error rate, whereas the ones where the hypothesis is 25% difference in time trends display the power of the test. For the control group, the means and SDs of mood scores were based on previous perinatal studies of longitudinal Edinburgh Postnatal Depression Scale scores [40] and assumed to be normally distributed. For the prepartum + postpartum intervention group, the test scores are assumed to be gradually decreasing over time with a maximal difference of 25% with respect to the controls. For the postpartum probiotic intervention group, the effect was assumed to have the same kinetics but with onset at birth. The correlation between study sessions was assumed to be 0.5.

The trial has 2 primary outcome variables (EPDS and STAI scores) and 2 primary group comparisons (prepartum + postpartum intervention vs placebo control and postpartum-only intervention vs placebo control). Thus, the false positive rate controlled at 5% level is as follows: α / 4 = 0.0125 (for each combination of a primary outcome variable and a group comparison). The time trends for comparing prepartum + postpartum intervention versus control (session 2-session 6; Table 1) and for comparing postpartum-only intervention versus control (session 3-session 6; Table 1) are modeled by 2 separate mixed models where baseline scores (session 1; Table 1), time point (considered a categorical variable), treatment, and the interactions between the time point and treatment were fixed effects, and participant was included as a random effect (random intercept). A history of previous pregnancy complications will be added as a binary covariate to the model. The global test for time-trend differences between groups is a max-*t* test. For each group comparison, the multiplicity coming from comparison at multiple time points is dealt with by performing inference based on the joint distribution of the test statistics from the appropriate set of linear contrasts of the linear mixed model parameters (using the R library *multcomp*).

A simulation using R statistical software (version 3.6.1; R Foundation for Statistical Computing) showed a power of 50% to 70% for observing statistically different time trends when considering recruiting 60 individuals per group, after accounting for an expected dropout rate of 20%, representing 48 participants per group completing the study (Table 2).

With the substantially lower observed dropout rate of 2.7% compared with the initially anticipated 20%, more participants than expected have completed the study, and the power therefore is increased from this initial illustration. Although every effort has been made to obtain complete data sets, the mixed model used for analysis is robust against missing values and valid under missing at random. Outliers will be detected before unblinding, with appropriate action taken considering the medical context. The primary analysis will be an intention-to-treat analysis (considering all randomized participants who took at least 1 dose of the assigned product and provided postrandomization data) with a secondary per-protocol analysis planned. No interim analysis was performed for this trial.

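### Table 2's null simulations suggest that the four primary tests run mildly above their 0.0125 level (pooled 1.70%), and the 5% control claim does not address this

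*Protocol article*

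**What the plan says.** The Statistics section of the Protocol article defines the test family: "The trial has 2 primary outcome variables (EPDS and STAI scores) and 2 primary group comparisons". It then sets the level: "Thus, the false positive rate controlled at 5% level is as follows: α / 4 = 0.0125". Each of the four tests is a max-t test over visits from a mixed model with a random intercept for participant. For multiplicity over visits, the section describes this approach: "performing inference based on the joint distribution of the test statistics from the appropriate set of linear contrasts of the linear mixed model parameters". The software it names is the multcomp package in R.

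Table 2 reports 1000 simulations of this test. Its footnote says: "Rows where the hypothesis is null display the error rate". The null rows are:

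- EPDS: "Null Prepartum + postpartum probiotic vs placebo control 1.70" and "Null Postpartum-only probiotic vs placebo control 1.60"
- STAI: "Null Prepartum + postpartum probiotic vs placebo control 2.20" and "Null Postpartum-only probiotic vs placebo control 1.30"

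The footnote assumes a correlation of 0.5 between sessions. It takes control means and SDs from earlier perinatal EPDS studies but does not give their values. The text after the table says the calculation is for 48 completers per group. The section calls the study exploratory and the power calculations illustrative. It does not comment on the null rows, state the nominal level used to produce them, or report a familywise rate.

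**The concern.** A test run at 0.0125 should reject in about 1.25% of null simulations. All four rows are above that figure, and the article does not explain why. If the excess is real, the 5% claimed for the primary family is not the rate that the planned procedure delivers. A primary result just inside the cut-off would then carry somewhat more false-positive risk than stated. The power rows (72.0, 48.1, 69.2 and 50.3%) would be slightly flattered by the same critical value. The article says that this trial will be used to design and power a follow-up, so the calibration of these figures has a use beyond this report.

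**Working it through.** **Inputs.** From the Statistics section and Table 2: overall level 0.05; 2 outcomes × 2 comparisons; 1000 simulations; null rates 1.70, 1.60, 2.20 and 1.30%; 48 completers per group; session correlation 0.5. Assumed because the article does not say: Table 2 was run at 0.0125, the tests are two-sided, and the EPDS-STAI correlation lies between 0 and 0.9.

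**1. The plan's own figure.** 0.05 / (2 × 2) = 0.0125. It reproduces exactly.

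**2. Each null row against 1.25%.** The Monte Carlo standard error is √(0.0125 × 0.9875 / 1000) = 0.0035, or 0.35 points, and 12.5 rejections are expected per row. Exact binomial results:

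| Null row | Count | P(count this high or higher) | Exact 95% CI |
|---|---|---|---|
| EPDS, prepartum + postpartum | 17/1000 | 0.13 | 0.99 to 2.71% |
| EPDS, postpartum only | 16/1000 | 0.19 | 0.92 to 2.59% |
| STAI, prepartum + postpartum | 22/1000 | 0.009 | 1.38 to 3.31% |
| STAI, postpartum only | 13/1000 | 0.48 | 0.69 to 2.21% |

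Three intervals contain 1.25%. The fourth does not; after allowing for picking the largest of four, its p is 4 × 0.009 = 0.036.

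**3. Pooled.** 17 + 16 + 22 + 13 = 68, and 68/4000 = 1.70%. The expected count is 4000 × 0.0125 = 50. Treating rows as independent, the exact 95% CI is 1.32 to 2.15% and the one-sided p is 0.0085. Rows may be correlated through a shared placebo arm and shared participants. A check simulation of the stated design (20,000 runs) put the SD of the pooled count at 7.44 (EPDS-STAI correlation 0) to 8.90 (correlation 0.9). Then z = 18/7.44 = 2.42 down to 18/8.90 = 2.02, a one-sided p of about 0.01 to 0.02.

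**4. Familywise rate.** The sum is 1.70 + 1.60 + 2.20 + 1.30 = 6.80%, which is an upper bound. If the tests were independent it would be 1 − (0.983 × 0.984 × 0.978 × 0.987) = 6.6%. With correlation 0.5 between the two comparisons (shared placebo arm, equal groups), a Gaussian-copula calculation gives:

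| EPDS-STAI correlation (assumed) | Familywise rate from Table 2's rows | Familywise rate if each test held 1.25% |
|---|---|---|
| 0 | 6.3% | 4.7% |
| 0.5 | 5.9% | 4.4% |
| 0.7 | 5.5% | 4.1% |
| 0.8 | 5.2% | 3.9% |
| 0.9 | 4.7% | 3.5% |

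**5. Where an excess could come from.** Null simulations of a baseline-adjusted random-intercept model, with a normal reference at 0.0125 and session correlation 0.5, gave about 1.2 to 1.4% per test when all visits have the same SD. With equal SDs at 48 per group, the familywise rate was 5.0% (EPDS-STAI correlation 0) to 3.9% (correlation 0.9). When visit SDs were assumed to rise 1.25- to 1.5-fold, the per-test rate was about 1.4 to 2.2%, including at 60 per group. The random-intercept model imposes one common variance over visits, so unequal SDs could produce rates like those in Table 2.

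**The case against.** The strongest reply has four parts.

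- **The quoted sentence contains no arithmetic error.** 0.05/4 is a correct Bonferroni split. This stands.
- **The evidence is thin.** With 1000 runs, three rows are within Monte Carlo error, and 13 rejections against 12.5 expected is nominal. This stands row by row. It does not dispose of the 2.20% row or of the pooled rate, which remain unlikely at a true 1.25%.
- **The mechanism is not documented.** The article gives no visit SDs and names the multcomp library without its degrees of freedom. With equal SDs the stated design is close to nominal. This stands too: unequal variances are a likely cause, with a smaller contribution if a large-sample normal reference is used, but neither is established.
- **The study is exploratory, Table 2 is called illustrative, and such detail often sits in an SAP.** This lowers the severity. However, the article itself states the random-intercept model, the error rates and the 5% control, so the mismatch is among things it chose to report.

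A reader might infer that the true overall error is 6.8%. The documents do not support that: 6.8% ignores the overlap between tests that share a placebo arm and the same women. Nor do they show that 5% control is refuted. At a high enough EPDS-STAI correlation, the slack in the Bonferroni split absorbs the excess.

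Better retention (179 completers, about 60 per group) may also be offered as an answer. More participants help a normal reference, but they do not reliably remove an excess caused by a wrong variance structure.

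**Conclusion.** The point holds as a moderate one. Table 2 suggests that the planned test rejects at about 1.7% rather than 1.25% per comparison under the null, a ratio of 1.70/1.25 = 1.36, and the article claims 5% control without addressing it. The implied familywise rate is about 4.7 to 6.3%. This rests on three assumptions: that Table 2 was run at 0.0125 (the only per-test level the article gives), that the comparisons correlate at 0.5, and that the EPDS-STAI correlation is between 0 and 0.9. The practical effect is confined to results near the cut-off and a slight overstatement of power. The power rows cannot be recomputed because the control means and SDs are not given.

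**What to change.** 1. Fit a covariance that allows visit-specific variances. Compute the max-t p-values from a multivariate t reference with small-sample degrees of freedom (Kenward-Roger or Satterthwaite).
2. State the nominal level behind Table 2's null rows.
3. Rerun the null simulation with at least 10,000 replicates, for a standard error of √(0.0125 × 0.9875 / 10,000) = 0.11 points instead of 0.35. Report the per-test and familywise rates directly, with the EPDS-STAI correlation stated.
4. If the excess persists, lower the nominal cut-off until it is gone, and restate the error and power rows of Table 2.
5. If none of this is done, qualify the 5% control claim.

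The cost is SAP wording and a rerun of existing simulation code, with slightly lower restated power. No new data are needed. The article reports no outcomes yet, so the change can be free of data-driven choice if it is fixed before unblinding.

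### The fixed 0.05/4 split over the four primary tests is valid but less powerful than Holm's step-down, which would add about 12 points of power to the weakest comparison if all four planned effects are real

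*Protocol article*

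**What the plan says.** The Statistics section of Methods states: "The trial has 2 primary outcome variables (EPDS and STAI scores) and 2 primary group comparisons". The comparisons are prepartum + postpartum probiotic against placebo and postpartum-only probiotic against placebo. With "the false positive rate controlled at 5% level", the article gives each of the four tests a fixed share: "α / 4 = 0.0125 (for each combination of a primary outcome variable and a group comparison".

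Each test is a max-t test over the session-wise treatment contrasts of a mixed model. The joint-distribution adjustment (R library *multcomp*) handles the several time points within one group comparison. Nothing in the section passes alpha from one of the four tests to another.

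Table 2 gives illustrative powers for a maximal 25% difference:

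- EPDS: 72.0% (prepartum + postpartum) and 48.1% (postpartum-only).
- STAI: 69.2% and 50.3%.

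The text summarises these as follows: the simulation "showed a power of 50% to 70% for observing statistically different time trends", with 60 recruited and 48 completing per group.

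**The concern.** Under a fixed split, a test must reach 0.0125 even when the other three hypotheses have already been rejected. Holm's procedure compares the ordered p-values with 0.05/4, 0.05/3, 0.05/2 and 0.05, and stops at the first failure. It rejects everything that the fixed split rejects and sometimes more. It needs no assumption about how the four tests are correlated and keeps the same 5% familywise guarantee for them.

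The loss falls mainly on the postpartum-only comparison, which has the lowest planned power (48% to 50%). That comparison answers one of the study's stated questions: whether starting after delivery is still beneficial.

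**Working it through.** **1. The plan's own figures.**

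- Alpha: 2 outcomes × 2 comparisons = 4 tests, and 0.05/4 = 0.0125. Reproduced.
- Completers: 60 × (1 − 0.20) = 48 per group. Reproduced.
- Powers: Table 2 cannot be rebuilt, because the control means, the SDs and the exact course of the effect are not printed. A max-t model with 48 per group, session correlation 0.5 and a linear effect was set to 72% for EPDS prepartum + postpartum. It gives 67% for postpartum-only if the full 25% is reached by 12 weeks, and 15% if the same slope starts at birth. The stated 48.1% lies between these, so it is taken as given. Its simulation error is √(0.481 × 0.519/1000) = 1.6 points.
- Level: Table 2's null rows (1.70, 1.60, 2.20 and 1.30%) average 1.7%. This is of the order of 1.25% and supports reading the powers as computed at 0.0125. They may be slightly optimistic.

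**2. Convert each power to a noncentrality** (two-sided tests assumed): δ = z(1 − 0.0125/2) + z(power), with z(0.99375) = 2.498.

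| Test | Power at 0.0125 | δ |
|---|---|---|
| EPDS, prepartum + postpartum | 72.0% | 3.08 |
| EPDS, postpartum-only | 48.1% | 2.45 |
| STAI, prepartum + postpartum | 69.2% | 3.00 |
| STAI, postpartum-only | 50.3% | 2.51 |

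For the weakest test, the ceiling at the full 0.05 is Φ(2.45 − 1.96) = 68.8%.

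**3. Simulate both rules on four correlated statistics** (400,000 replicates per setting). The correlation between the two comparisons is 0.5, from the shared placebo arm and 1:1:1 allocation; 0 was also tried. The EPDS-STAI correlation is not stated, so it was varied from 0 to 0.9. With both correlations at 0.5 and all four effects real:

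| Test | Fixed 0.0125 | Holm |
|---|---|---|
| EPDS, prepartum + postpartum | 72.0% | 78.0% |
| EPDS, postpartum-only | 48.1% | 60.1% |
| STAI, prepartum + postpartum | 69.2% | 76.0% |
| STAI, postpartum-only | 50.3% | 61.8% |

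Over all the correlations tried, the gain for the weakest test was 11.4 to 12.6 points. Repeating the exercise with max-t statistics over 5 and 4 sessions, calibrated to the same powers, gave 60.0% to 60.5%. The chance of at least one rejection was 90.3% under both rules at correlations of 0.5. The two must agree, because Holm's first step uses 0.0125.

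**4. Scale to the 179 completers** (equal split assumed): δ × √(179/144) = 2.45 × 1.115 = 2.73. Power at 0.0125 is Φ(2.73 − 2.498) = 59%, and Holm gives 71.1% to 72.8%.

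**5. Relax the assumption that all four effects are real** (EPDS postpartum-only, 48 per group):

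| Effects that are real | Gain |
|---|---|
| All four | about 12 points |
| All except STAI postpartum-only | about 7 points |
| EPDS only, both comparisons | about 3 points |
| Postpartum-only arm, both outcomes | about 2 points |
| EPDS postpartum-only alone | about 0.1 point |

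**6. Familywise error of the four global tests.** Under the global null it was 4.1% to 4.7% and identical for both rules. Over all partial nulls, the largest value for Holm was 5.07% from 200,000 replicates, which is 5% within simulation error.

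**7. Session-level claims.** Assume a real effect only at session 6 in every family, session and EPDS-STAI correlations of 0.5, a shared placebo arm, and each session judged at its family's Holm level. Two separate runs put the chance of any false session-level claim at 3.5% to 3.7% under fixed 0.0125. Under Holm it was 5.2%, rising to 8.4% to 8.5% with large effects.

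**The case against.** The strongest reply is that nothing here is wrong. The fixed split controls what it says it controls, and the article calls the study exploratory, with unknown effect sizes and illustrative power. That stands as far as validity goes. It does not remove the point, because the section still commits to 5% control over four primary tests, and Holm meets that commitment with more power.

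A second reply is that the 12 points are conditional. This stands in full. A reader might take 12 points as what the split costs in any event. The documents do not support that: they assume all four effects only for planning, and the study itself asks whether starting after delivery works as well as starting before. Arms that respond differently are therefore a live possibility, and step 5 shows how quickly the gain then shrinks.

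A third reply is that the fixed split buys something. With 0.0125 per family, the session-wise contrasts in all four families are also jointly controlled at 5%. Holm over the global p-values does not keep this, as step 7 shows. The article does not say outright that session-level claims will be made. This reply therefore limits how Holm should be used and does not count against using it for the global tests. The fixed split also yields simultaneous intervals that match its decisions, which is useful in a trial meant to inform a follow-up.

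Lastly, 48% is the planning figure. The article reports 179 completers and says that power has risen, and step 4 puts the starting point nearer 59%. The gain there is still 12 to 14 points if all four effects are real.

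**Conclusion.** The fixed split is valid but inefficient for the four global max-t tests. When all four Table 2 effects are real, Holm raises power for EPDS postpartum-only from 48% to about 60% at 48 per group, and from about 59% to 71-73% at 179 completers. The other gains at 48 per group are 11 to 12 points for STAI postpartum-only and about 5 to 8 points for the two prepartum + postpartum tests. The gain for the weakest test falls to about 7, 3, 2 and 0 points as fewer of the other effects are real.

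The result rests on Table 2's powers being those at 0.0125, on two-sided tests, and on an assumed EPDS-STAI correlation, which moves the figure very little.

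Two stronger readings should be resisted. One is that the plan contains an error-rate fault; it does not. The other is that the fixed threshold gives no protection in return, or that Holm keeps the same error rate for every claim. The equality holds for the four global tests only. This is a worthwhile and cheap improvement, not a correction of a mistake, and it does not raise the chance of at least one positive finding.

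**What to change.** Before unblinding, specify in the analysis plan that the four global max-t p-values are tested by Holm's procedure. The ordered p-values are compared with 0.0125, 0.0167, 0.025 and 0.05, stopping at the first failure, and Holm-adjusted p-values are reported. State that the 5% familywise claim covers these four tests only. Keep any session-level claims and simultaneous intervals at the fixed 0.0125 per family.

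The article reports no outcomes and describes blinding until database lock of the primary outcome, so as written there was still time to make the change. It needs no further participants. The cost is that the intervals no longer correspond one-to-one with the step-down decisions: a hypothesis rejected at a later Holm step may have 0.0125-level intervals that all include no difference. Adjusted p-values should therefore stand beside the intervals, with a line of explanation.

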**Methods:**

This double-blind, placebo-controlled, randomized, and 3-parallel-arm study aimed to recruit 180 women to evaluate the efficacy of the probiotic taken either during pregnancy and post partum (from 28-32 weeks’ gestation until 12 weeks after delivery; n=60, 33.3%) or post partum only (from birth until 12 weeks after delivery; n=60, 33.3%) in comparison with a placebo control group (n=60, 33.3%). Participants consumed the probiotic or matched placebo in a drink once daily. Mood outcomes were measured using the State-Trait Anxiety Inventory and Edinburgh Postnatal Depression Scale questionnaires, captured electronically at baseline (28-32 weeks’ gestation) and during e-study sessions over 5 further time points (36 weeks’ gestation; 9 days post partum; and 4, 8, and 12 weeks post partum). Saliva and stool samples were collected longitudinally at home to provide mechanistic insights.

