### Randomization Procedure and Study Arms

This is a double-blind, placebo-controlled, randomized, and 3-parallel-arm study aimed at assessing time trends in perinatal mood and stress with ingestion of the probiotic BL NCC3001, starting from either the third trimester (28-32 weeks’ gestation) or immediately after birth until 12 weeks post partum, compared with placebo. The 3 arms are (1) prepartum + postpartum probiotic, (2) prepartum placebo + postpartum probiotic, or (3) prepartum + postpartum placebo in a 1:1:1 ratio (Figure 1). Participants were randomly allocated via an electronic database to 1 of these 3 arms at the first virtual study session when the participant was at 30 (allowed window 28-32) weeks’ gestation.

Until the database lock of the primary outcome, neither the investigator nor the participant nor the site team nor the independent monitor managing the study will know to which investigational product each participant was allocated, with the exception of specified delegated regulatory staff within Nestlé, the product manufacturing site, and the supply and quality managers at the sponsor’s clinical research unit.

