						Session 1: gestation 30 weeks (+2 or −2 weeks)		Session 2: gestation 36 weeks (+2 or −2 weeks)		Session 3: post partum 9 days (+5 or −5 days)		Session 4: post partum 4 weeks (+7 or −7 days)		Session 5: post partum 8 weeks (+7 or −7 days)		Session 6: post partum 12 weeks (+7 or −7 days)
Informed consent				✓												
Inclusion and exclusion criteria				✓												
HADS^a^				✓						✓						✓
Demographics				✓												
Obstetric history				✓												
Medical history				✓												
Randomization						✓										

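### The postpartum-only comparison leaves the 36-week mood scores unused, although both of its arms are still on the same placebo then; this costs precision, not validity

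*Protocol article*

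**What the plan says.** Randomization Procedure and Study Arms defines the two arms of this comparison: "2) prepartum placebo + postpartum probiotic, or (3) prepartum + postpartum placebo in a 1:1:1 ratio". Arm 2 takes placebo until delivery and arm 3 takes placebo throughout, and participants and site staff are blinded. The Intervention section describes a single placebo.

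Table 1 places "Session 2: gestation 36 weeks" (window 2 weeks either side) under pregnancy and ticks both EPDS and STAI at that visit. The abstract agrees: scores are captured at baseline and "during e-study sessions over 5 further time points", the first of them at 36 weeks.

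The Statistics section fixes the primary model: the time trends "for comparing postpartum-only intervention versus control (session 3-session 6; Table 1) are modeled by 2 separate mixed models where baseline scores (session 1; Table 1") enter as a fixed effect. Outcomes in this comparison therefore start after birth, and session 1 is the pre-treatment adjustment. One other covariate is named: "A history of previous pregnancy complications will be added as a binary covariate to the model". Each combination of outcome and comparison is tested by max-*t* at 0.05/4 = 0.0125.

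Table 2 gives the postpartum-only comparison 48.1% power (EPDS) and 50.3% (STAI). The prepartum + postpartum comparison has 72.0% and 69.2%.

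**The concern.** A score taken after randomization is normally kept out of the covariate set because treatment may have changed it. That reason is absent here. Until birth, arms 2 and 3 receive the same product under blinding, so for this contrast the 36-week score is as much a pre-treatment measurement as the one at 28-32 weeks. It is also nearer in time to the postpartum outcomes.

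The article states which sessions are outcomes and which session is the baseline, so this is a choice made in the primary model and not a detail left open. Its result is that a prognostic score already collected on both primary scales goes unused in the comparison with the lower stated power. That comparison addresses one of the trial's stated questions: whether a benefit remains if the probiotic is started only after delivery.

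**Working it through.** **Inputs from the document.** Correlation between sessions 0.5. Per-test alpha 0.0125. 60 randomized and 48 completing per arm. Max-*t* over sessions 3-6 (four contrasts). Stated powers 48.1% and 50.3%.

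**Assumptions.** Two-sided testing (sidedness is not stated), equal correlation between all sessions, normal scores, and an effect that grows linearly from birth to its maximum at 12 weeks. A constant effect is used as an alternative.

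**The plan's own figures.**
- 0.05/4 = 0.0125, and 60 × 0.8 = 48. Both reproduce exactly.
- The powers in Table 2 cannot be rebuilt, because control means, SDs and exact kinetics are not given.
- As a plausibility check, I set a linear effect to give the stated 72.0% for the prepartum + postpartum arm. The postpartum-only power is then about 15% if the slope is the same, and about 67% if the same maximum is reached by 12 weeks. The stated 48.1% lies inside that range, so Table 2 is not contradicted.

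**Residual variance.** With *k* pre-treatment scores and common correlation ρ, the variance of a later score given those scores, relative to its total variance, is

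v(k) = 1 − kρ² / [1 + (k − 1)ρ].

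At ρ = 0.5:
- Session 1 only: v(1) = 1 − 0.25 = 0.750.
- Sessions 1 and 2: v(2) = 1 − 2(0.25)/1.5 = 0.667.
- Ratio 0.667/0.750 = 0.889, so variance is 11% lower. The standard error ratio is √0.889 = 0.943, or 5.7% smaller.
- Equivalent sample size: 0.750/0.667 = 1.125, so 48 per arm act like 54.

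**Power.** The effect was set to give the stated power with one pre-treatment score at 48 per arm. Power was then recomputed with two scores at the same alpha.

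| ρ = 0.5, linear effect | Session 1 only | Sessions 1 and 2 |
|---|---|---|
| EPDS, 48 per arm | 48.1% (calibrated) | about 55.5% |
| STAI, 48 per arm | 50.3% (calibrated) | about 58% |
| EPDS, 60 per arm | about 61% | about 69% |
| STAI, 60 per arm | about 63% | about 71% |

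The gain is about 7-8 points; with a constant effect it is nearer 9.

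**Sensitivity to the correlation.**
- ρ = 0.3: v falls from 0.910 to 0.862 (ratio 0.947). Power goes from 48.1% to about 52%.
- ρ = 0.7: v falls from 0.510 to 0.424 (ratio 0.830). Power goes from 48.1% to about 60%.
- Over both scales, both sample sizes and both effect shapes, the gain is about 4 to 14 points.

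**Error rate.** In 10,000 simulated trials of the random-intercept analysis at one fixed effect, power was 61.5% with one score and 68.5% with two. Rejection under the null was 1.3% and 1.2%, so the gain does not come from a looser test.

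**The case against.** The strongest reply is that nothing here is wrong. Adjusting for the score at the randomization visit is conventional, it gives both comparisons the same covariate set, and the trial is described as exploratory with illustrative power. All of that is true. It shows that the plan is valid, but not that there is a reason to set aside a collected pre-treatment score.

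The size of the gain also depends on quantities the article does not give. If the effect is calibrated to 72.0% in the other comparison, the gain runs from about 3 points (15% to 18%, same slope) to about 8 (67% to 74%, same maximum). The direction and, at ρ = 0.5 with equal correlations, the 11% are firm; the power points are approximate.

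Four stronger readings are tempting, and the document does not support them:
- *That the comparison is biased.* It is not: session 1 adjustment in randomized arms is sound.
- *That session 2 should be among the tested contrasts.* No treatment difference can exist then, and adding it would only put a null contrast into the max-*t*.
- *That the comparison now has 48-50% power.* Those figures are for 48 completers per arm. The article reports 2.7% dropout, 179 completers (179/3 is about 60 per arm) and power above the illustration.
- *That arm 2 should also be pooled with arm 3 as placebo at session 2 for the prepartum + postpartum comparison.* The variance of that one contrast would fall by a quarter, (1/60 + 1/120)/(2/60) = 0.75. But it is the earliest contrast and, under the plan's gradual effect, the smallest: power moves from 72.0% to 72.1-72.6%. It would also replace the two-model structure. It is not worth proposing.

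**Conclusion.** The point holds as a loss of precision in a valid analysis. For the postpartum-only comparison, session 2 is a second pre-treatment measurement of both primary scales, and the stated model does not use it. At the plan's correlation of 0.5, this forgoes an 11% reduction in residual variance, worth 12.5% more women per arm and about 7-8 power points at either 48 or 60 per arm.

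The figures rest on equal correlation between sessions, two-sided testing and an assumed effect shape. If correlations fade with time instead, the benefit would be largest at session 3 and smallest at session 6. The gain was positive at every correlation and effect shape tried. The change is worth making because it needs no new data, but the planned result would stand without it.

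**What to change.** Before unblinding, amend the postpartum-only model so that session 1 and session 2 scores both serve as pre-treatment information. The preferred form enters session 2 as a pre-treatment outcome with one mean shared by the two arms. Women who deliver before session 2 (window 34-38 weeks) then stay in the analysis; a plain second covariate would drop them unless a rule for the missing score is added. Keep the tested contrasts at sessions 3-6, and leave the prepartum + postpartum model as it is.

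The article reports that data processing is ongoing with no outcomes yet, and that the blind holds until database lock of the primary outcome. If the blind has since been broken, report the two-score model as a labelled sensitivity analysis beside the planned one.

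The cost is an amendment to a stated primary analysis, which needs a date and a reason on record, and a slightly different set of pre-treatment scores in the two models. No further data are needed.
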